**Fig. 3 Fig3:**
[figure not shown]
The BATTLE-AMI study *flowchart*. After fibrinolytic therapy performed in the 6 h after onset of symptoms, subjects with STEMI will be referred to the hospital for coronary angiography and PCI, if necessary. Those patients admitted to the hospital within 24 h of STEMI will be randomized to one of the four assignments in a 1:1:1:1 ratio (ticagrelor/rosuvastatin, ticagrelor/simvastatin plus ezetimibe, clopidogrel/rosuvastatin, or clopidogrel/simvastatin plus ezetimibe). Blood, urine, and feces samples will be collected at baseline, 30 days, and 180 days for metabolomics, proteomics, microbiota, and flow-cytometry studies. cMRI studies will be performed during peri-hospitalization period and at 30 and 180 days

Our main hypothesis is that rosuvastatin/ticagrelor will be superior than simvastatin plus ezetimibe/clopidogrel, for the cMR parameters. Additionally, the pilot study indicated that the ezetimibe/clopidogrel was similar to simvastatin plus ezetimibe/ticagrelor and rosuvastatin/clopidogrel combinations regarding the primary endpoint and we decided to compare those other groups (rosuvastatin/clopidogrel and simvastatin plus ezetimibe/ticagrelor) to explore possible mechanisms for the primary and secondary objectives.

Thereafter, our sample size derivation was done considering that rosuvastatin/ticagrelor will improve mean cMRI LVEF by 6% compared to each of the other three groups, assuming a 13% dropout rate. The alpha level fixed in 0.05/3 (1.67%) was considered to adjust the global alpha error in 5% using Dunnett’s test approach (many-to-one comparisons).

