**Methods/design:**

BATTLE-AMI is an open-label, randomized trial comparing the effects of four therapeutic strategies (rosuvastatin/ticagrelor, rosuvastatin/clopidogrel, simvastatin plus ezetimibe/ticagrelor, or simvastatin plus ezetimibe/clopidogrel) on infarcted mass and left ventricular ejection fraction (LVEF) (blinded endpoints) in patients with ST-segment elevation myocardial infarction submitted to fibrinolytic therapy before coronary angiogram (pharmacoinvasive strategy). All patients (n = 300, 75 per arm) will be followed up for six months. The effects of treatment on subsets of B and T lymphocytes will be determined by flow-cytometry/ELISPOT and will be correlated with the infarcted mass, LVEF, and microcirculation perfusion obtained by cardiac magnetic resonance imaging. The primary hypothesis is that the combined rosuvastatin/ticagrelor therapy will be superior to other therapies (particularly for the comparison with simvastatin plus ezetimibe/clopidogrel) for the achievement of better LVEF at 30 days (primary endpoint) and smaller infarcted mass (secondary endpoint) at 30 days and six months. The trial will also evaluate the improvement in the immune/inflammatory responses mediated by B and T lymphocytes. Omics field (metabolomics and proteomics) will help to understand these responses by molecular events.

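### The per-comparison level 0.05/3 is attributed to Dunnett but is Bonferroni's, and the article does not settle whether one comparison or three are confirmatory

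*Protocol article*

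**What the plan says.** All of the following is in the Protocol article.

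- **Level and method** (Study design and objectives, text after Fig. 3): "The alpha level fixed in 0.05/3 (1.67%) was considered to adjust the global alpha error in 5" per cent, "using Dunnett’s test approach (many-to-one comparisons").
- **Sizing** (same paragraph): the assumption is that "rosuvastatin/ticagrelor will improve mean cMRI LVEF by 6% compared to each of the other three groups", "assuming a 13% dropout rate".
- **Main hypothesis** (paragraph just before): "Our main hypothesis is that rosuvastatin/ticagrelor will be superior than simvastatin plus ezetimibe/clopidogrel". The rosuvastatin/clopidogrel and simvastatin plus ezetimibe/ticagrelor groups are compared "to explore possible mechanisms for the primary and secondary objectives".
- **Abstract, Methods/design**: the primary hypothesis is that "the combined rosuvastatin/ticagrelor therapy will be superior to other therapies", with a parenthesis that stresses the comparison with simvastatin plus ezetimibe/clopidogrel.
- **Primary objective** (Study design and objectives, opening paragraph): a comparison of the different therapies on 30-day LVEF, with no pair singled out.
- **Size** (Abstract): "All patients (n = 300, 75 per arm) will be followed up for six months". Allocation is 1:1:1:1 (Study population and randomization).

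The article does not give the SD of LVEF, the target power or whether tests are one- or two-sided.

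**The concern.** There are two separate faults.

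**Method and number do not match.** Dunnett's procedure uses the correlation between contrasts that share a comparator arm and so allows a level somewhat above 0.05/3. A comparison with p between 0.0167 and 0.0189 would succeed under the method named and fail under the number printed.

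**The confirmatory family is not settled.** The main-hypothesis paragraph points to one confirmatory comparison with two supporting ones. The sizing paragraph treats three comparisons alike. The abstract can be read as requiring superiority over every other arm. Success could therefore mean winning the main comparison, winning any one, or winning all three. If this stays open, the claim could be chosen after the results are known. The choice also matters for efficiency: if only the main comparison is confirmatory, giving it one third of the alpha is unnecessary.

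**Working it through.** **Inputs from the article.** Three comparisons against rosuvastatin/ticagrelor; 75 per arm; dropout 13%; difference of 6, read as LVEF percentage points; equal allocation.

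**Assumptions.** Two-sided tests; SD as shown below, because none is given.

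**1. The plan's own figures.** 0.05/3 = 0.01667, which is the stated 1.67% and is Bonferroni's division. Evaluable patients: 75 × 0.87 = 65.25, so about 65 per arm. Conversely 65/0.87 = 74.7, rounded up to 75, which agrees with 300 in total. Error degrees of freedom: 4 × (65 − 1) = 256.

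**2. Dunnett's level.** With equal arms, any two contrasts sharing the rosuvastatin/ticagrelor arm correlate at 0.5. The critical value c solves P(max |T| > c) = 0.05 for three such t statistics. By numerical integration:

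| Rule (two-sided, 256 df) | Critical t | Level per comparison | Family-wise error |
|---|---|---|---|
| Dunnett, 3 comparisons | 2.363 | 0.0189 | 5.0% |
| 0.05/3 | 2.410 | 0.0167 | 4.4% |

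With 75 per arm (296 df) Dunnett's level is still 0.0189.

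**3. Cost of the mismatch.** Power ≈ Φ(6/(SD × √(2/65)) − z(1 − α/2)). The SD that gives 80% power at 0.0167 with 65 per arm is 10.57; the SD that gives 90% is 9.31. Moving from 0.0167 to 0.0189 changes power from 80.0% to 81.3% and from 90.0% to 90.8%. In sample size this is 64 rather than 65 evaluable per arm, or 74 rather than 75 enrolled.

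**4. Effect of the equal split on the main comparison.**

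| Assumed SD | Power at 0.05/3 | Power if tested first at 0.05 | Difference (points) |
|---|---|---|---|
| 9.31 | 90.0% | 95.7% | 5.7 |
| 10.57 | 80.0% | 89.9% | 9.9 |
| 12 | 67.6% | 81.3% | 13.7 |

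Worked line for SD 10.57: standard error 10.57 × √(2/65) = 1.854; 6/1.854 = 3.236; 3.236 − 2.394 = 0.842, giving 80%; 3.236 − 1.960 = 1.276, giving 90%. Over the wider range SD 8 to 14 the difference runs from 2 points (97.0% to 99.0%) to about 17 (52.0% to 68.6%).

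**5. A hierarchy for all three.** Test the main comparison at 0.05 and, if it succeeds, the other two with a two-comparison Dunnett (level 0.027 each). By simulation at SD 10.57, with a true 6-point gain over each arm, each second-step comparison has 79% power (80% at 0.05/3). Power to win all three rises from 61% to 71%.

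**The case against.** The strongest reply has four parts.

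- **The figure is in the sample-size derivation.** Nowhere does the article say that final p-values will be judged against 0.0167. Sizing at Bonferroni's level and analysing with Dunnett is workable and slightly cautious, and the analysis plan, which is not shown, may say so. This stands. A reader might infer that 0.05/3 is the threshold that decides the trial; it is only the one confirmatory level that the article prints.
- **Control is not lost.** A reader might take the mismatch to mean that the 5% error rate is breached. It is not: 4.4% is below 5%. This stands, and makes the first fault one of labelling.
- **No planned power is lost.** A reader might infer that the main hypothesis is underpowered. The sizing text uses 0.0167 for a 6-point gain over each arm, so nothing shows power below its target. The gains above are relative to an alternative testing order and rest on an assumed SD. This stands too.
- **Equal many-to-one testing is legitimate.** It allows any single comparison to be claimed, which a hierarchy does not. The article never labels the other two tests non-confirmatory; its phrase about mechanisms may only say why those arms are compared. The abstract, too, emphasises the same main pair, and the pilot finding that the comparator arms were similar is a reason to treat them alike.

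The last part justifies either design but does not reconcile the text. One main hypothesis with mechanistic companions and three equally weighted confirmatory tests are different plans, and the article describes both. The complaint concerns conflicting printed statements, so an analysis plan elsewhere does not remove it.

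**Conclusion.** The point holds in a limited form. The article attributes to Dunnett a level that is Bonferroni's; the discrepancy (0.0167 against 0.0189, two-sided, about 65 per arm) is conservative and worth about one power point. The more consequential fault is that the article is inconsistent on whether one comparison or three are confirmatory.

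If the main comparison alone is the confirmatory one, testing it first at the full 0.05 would add about 6 to 14 power points for SD 9.3 to 12 (about 80% to 90% at SD 10.6). That size depends on an SD and two-sidedness that the article does not state. If three co-equal comparisons are intended, the equal split is sound and only the wording and the label need correcting.

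**What to change.** 1. **Choose one confirmatory family** and state it identically in the abstract, the primary objective, the main-hypothesis paragraph and the sample-size paragraph.
2. **Make number and method agree.** Either use Dunnett-adjusted p-values (about 0.0189 per comparison, two-sided, at 65 evaluable per arm) or keep 0.05/3 and call it Bonferroni.
3. **If the main comparison is the confirmatory one**, test rosuvastatin/ticagrelor against simvastatin plus ezetimibe/clopidogrel first at two-sided 0.05 and, only if it succeeds, the other two with a two-comparison Dunnett (p < 0.027 each). Say that superiority over all other therapies may be claimed only if all three succeed.
4. **If all three are co-equal**, keep Dunnett and remove the wording that singles out one main hypothesis and describes the others as exploring mechanisms.

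**Cost.** No added patients or data. The hierarchy gives up any claim on the other two comparisons when the first fails. The Trial status section reports recruitment under way since May 2015 in an open-label trial, so changing the testing order is a substantive amendment and should be dated and documented before any treatment comparison is seen. Correcting the label alone is a wording change.

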### Study organization

The steering committee of the study is composed of representatives from the Universidade Federal de São Paulo (UNIFESP, São Paulo, Brazil), Instituto Dante Pazzanese de Cardiologia (IDPC, São Paulo, Brazil), and Research Institute, Hospital do Coração (HCor, São Paulo, Brazil). An independent data safety monitoring board was constituted by representatives of the Heart Institute (InCor, São Paulo, Brazil) and is planned to analyze data three times during the study to evaluate only safety measures (serious adverse events, such as bleeding, acute kidney injury, new myocardial infarction, and mortality). Based on those parameters, the board may consider removing an intervention arm or study’s early termination by safety reasons or LVEF data. Those comparisons will consider Haybittle-Peto boundary (*p* < 0.001).

### Laboratory analyses

Microparticles and endothelial progenitor cells will be determined by flow-cytometry using specific markers [25–27]. Subsets of B and T lymphocytes will be evaluated by flow-cytometry and IgM and interleukins released by specific B and T cells will be quantified by ELISA for cytokine evaluation and ELISPOT for IgM detection [28]. Metabolomics and proteomics in plasma and urine will be determined by LC-MS/MS or CE-MS technique [29]. A methodology for targeted and untargeted metabolomics will be evaluated by using a pool of bio fluids (urine and plasma) with some (*n* = 10) healthy people. All samples will be submitted to a protein precipitation procedure, to guarantee method repeatability and preserve the chromatographic column. After protein precipitation, the supernatant will be dried followed by addition of a proper solvent and analyzed by LC-MS/MS or CE-MS. For untargeted metabolomics, in order to evaluate possible sources of variation during analysis, Quality control samples (QC) will be processed, which consist of a pool of 5 μL of each sample (control and treated). Thus, the QCs will be injected five times in the beginning of the batch, between every five injections and three at the end of the batch, and for the targeted metabolomics method, standards and internal standards will be used.

All data obtained for untargeted metabolomics will be processed by specific software and all significant metabolites will be obtained after statistical analysis by SIMCA 14 software (Umetrics, Umea, Sweden) by multivariate analysis. All putative metabolites will be analyzed by using the HMDB and METLIN free databases followed by KEGG pathway evaluation. Otherwise, the protein pellet obtained will be dissolved and the proteins digested according to a well-established procedure [29, 30]. For proteomics, all peptides will be detected by LC-MS/MS and identified using specific programs to proteomics field. The proteins differentially expressed in the four groups, including the three visits, will be compared.

Microbiota will be analyzed by new-generation sequencing techniques followed by bioinformatics analyses [31].

### Cardiac magnetic resonance images

The amount of infarcted mass, LVEF, and microcirculation will be determined by 3-T cMRI. For left ventricular function, cMRI images will be acquired using a 3-T scanner. Patients will be positioned in the supine position with a phased-array coil placed over the thorax. Repeated breath-holds and gating to the electrocardiogram will be applied to minimize the influence of cardiac and respiratory motion on data collection. Cine cMRI will be performed using a steady-state free-precession technique (fast imaging employing steady-state acquisition). We will obtain cine images in the two-chamber, four-chamber, left ventricular outflow tract, and short-axis views, the later with the first slice positioned at the basis covering the mitral valve and the last slice covering the apex, resulting in 10–12 cine breath-hold short-axis images to cover the entire left ventricle. Ischemia detection will be performed using first-pass perfusion imaging in the short-axis orientation only, with at least three slices (the maximum number of slices will be limited by heart rate). Infarction detection and quantification images will be acquired using the myocardial delayed enhancement technique, after the injection of a commercially available gadolinium-based contrast agent, administered intravenously at a dose of 0.15 mmol per kilogram of body weight. Contrast-enhanced images will be acquired in the same views as those used for cine MRI, with the use of a segmented inversion-recovery sequence. Each patient study will be reviewed by two independent blinded readers using dedicated software. LV function will be calculated using cine images to measure LVEF, volumes, and mass according to standard methods. Perfusion defects will be determined solely by subjective visualization. Perfusion defects will be defined as focal regions of myocardium that had diminished and/or delayed contrast enhancement compared with normal myocardium. For each patient study, each reader will report the likelihood of myocardial ischemia on a scale of 1 to 3: 1 = definitely normal; 2 = possibly abnormal; and 3 = definitely abnormal. Delayed-enhancement images will be used for infarct characterization. Myocardial tissue for each patient will be classified as hyper-enhanced (scar tissue) or normally enhanced myocardium after the observer, through manual interaction, defined a region of interest (ROI) within remote non-infarcted territory. The endocardial and epicardial borders will also be defined by manual interaction. Hyper-enhanced tissue is defined as areas with a signal intensity of > 2 standard deviations from the mean signal intensity measured in remote areas within the manually predefined ROI.

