**Discussion:**

BATTLE-AMI is aimed to (1) evaluate the role of subsets of lymphocytes on microcirculation improvement and (2) show how the choice of statin/antiplatelet therapy may affect cardiac remodeling after acute myocardial infarction with ST elevation.

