### Microcirculation and the role of ticagrelor/rosuvastatin

In addition to its antiplatelet properties via P2Y12 receptor antagonism, ticagrelor (but not clopidogrel) increases adenosine plasma levels in individuals with acute coronary syndromes [16]. An increase in adenosine concentration following ticagrelor use seems related to the inhibition of the adenosine transporter ENT1 (type 1 equilibrative nucleoside transporter) [17]. This effect of ticagrelor increases coronary blood flow and might be important in the early protection of the ischemic tissue in the acute phase of MI [18].

Rosuvastatin is an active substrate for hydroxymethylglutaryl-Coenzyme A reductase, decreasing the pathway of endogenous cholesterol synthesis. However, pleiotropic effects of statins seem to be mediated by the inhibition of isoprenoids, such as farnesylpyrophosphate and geranylgeranyl pyrophosphate, intermediate substances in the endogenous cholesterol synthesis, required for post-translational changes of small proteins. Consequently, there is a decrease in the intracellular signaling mediated by Rho GTPases. Decrease in Rho protein is followed by increased bioavailability of nitric oxide, promoting vasodilation [19]. Simvastatin is a prodrug that needs metabolization via cytochrome P450, isoenzymes 3A4. Only after this step, the formed metabolites serve as substrates for the hydroxymethylglutaryl CoA reductase, allowing the inhibition of cholesterol synthesis and promoting pleiotropic effects. However, thyenopyridines are also substrates for the same microsomal isoenzymes and some degree of pharmacokinetic interaction can be expected [20, 21]. Thus, another hypothesis of the BATTLE-AMI study is that by acting synergistically, the use of ticagrelor plus rosuvastatin could promote greater improvement in the microcirculation (Fig. 2). Previous studies have shown that the use of high-dose statin decreases biomarkers of myocardial damage in patients undergoing cardiac percutaneous coronary intervention, suggesting early improvement in microcirculation [22, 23].

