## Discussion

The BATTLE-AMI study will address important topics in the treatment of STEMI after a pharmacoinvasive strategy. First, the trial will examine whether the use of rosuvastatin/ticagrelor will be followed by improvement in the LVEF and smaller infarcted mass. The mechanisms involved will be examined by metabolomics and proteomics, including the measurement of adenosine. Second, the trial will evaluate the role of subsets of lymphocytes in the final infarcted mass and ventricular remodeling, exploring B and T cells phenotypes. For this analysis, the absolute number of subtypes of lymphocytes will be correlated with cMRI parameters as well as with those parameters obtained in the coronary angiogram. We expect that increased number of lymphocytes of more inflammatory phenotypes will be related to reperfusion injury, thus influencing the final infarcted mass and LVEF at 30 days post MI. Third, the effects of microbiota on the cMRI parameters and lymphocytes differentiation will be examined. We expect that the presence of a pathological microbiota may contribute to lymphocyte phenotype differentiation. Finally, the relationship among microparticles derived from endothelium, platelets, and leukocytes with the cMRI parameters will be addressed. This analysis will test the relevance of these new vascular biomarkers in the coronary heart disease and possible influences of the treatments. Thus, the trial will review the role of two major players considered to be involved with ventricular remodeling and infarcted mass size: inflammation and microcirculation under highly effective lipid lowering therapies.

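### After the first 24 hours, microcirculation is measured only by a subjective three-point ischemia-likelihood score that does not grade the extent of a defect

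*Protocol article*

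**What the plan says.** Several sections make microcirculation something to be measured and related to other variables.

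- Abstract, Methods/design: treatment effects on B and T lymphocyte subsets "will be correlated with the infarcted mass, LVEF, and microcirculation perfusion obtained by cardiac magnetic resonance imaging".
- Abstract, Discussion: the first aim is to "evaluate the role of subsets of lymphocytes on microcirculation improvement".
- Microcirculation and the role of ticagrelor/rosuvastatin: the hypothesis is that "the use of ticagrelor plus rosuvastatin could promote greater improvement in the microcirculation".
- Discussion: the trial reviews "two major players considered to be involved with ventricular remodeling and infarcted mass size: inflammation and microcirculation".

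The section Cardiac magnetic resonance images then fixes the instrument and the readout. "The amount of infarcted mass, LVEF, and microcirculation will be determined by 3-T cMRI". "Ischemia detection will be performed using first-pass perfusion imaging in the short-axis orientation only, with at least three slices". Perfusion defects are judged by eye only, and for each patient study "each reader will report the likelihood of myocardial ischemia on a scale of 1 to 3", where 1 is definitely normal, 2 possibly abnormal and 3 definitely abnormal. For delayed enhancement, "Myocardial tissue for each patient will be classified as hyper-enhanced (scar tissue) or normally enhanced myocardium", using a threshold of 2 standard deviations against remote myocardium.

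Angiographic analysis adds blush grade and TIMI frame count as measures of tissue-level perfusion, taken at the angiogram in the first 24 hours. The legend of Fig. 3 places the MRI scans around the hospital stay and at 30 and 180 days.

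**The concern.** Correlation and improvement both need a quantity that can be larger or smaller. The score records a reader's certainty that ischemia is present. A small definite defect and a large definite defect both score 3, and a defect that shrinks but stays visible does not change its score. All participants have documented STEMI, and a defect is any focal region of reduced or delayed enhancement, so clustering in the top category is plausible, although the article gives no distribution.

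The delayed-enhancement map does not fill the gap. It gives the extent of infarct, not of impaired perfusion. At stake are the mechanistic analyses: whether treatment changes microcirculation, and whether lymphocyte subsets track it at 30 and 180 days.

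**Working it through.** **Which perfusion measures exist, and when**

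| Measure | Section | Graded for extent or degree? | Time |
|---|---|---|---|
| Blush grade, TIMI frame count | Angiographic analysis | Yes | First 24 h |
| 1 to 3 likelihood score | Cardiac magnetic resonance images | No, grades certainty | Around hospital stay, 30 and 180 days |
| Scar or normal map | Cardiac magnetic resonance images | Infarct extent, not perfusion | Same scans |

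Study population and randomization places randomization before the angiogram and within the first 24 hours. The graded measures therefore reflect little treatment exposure and no later change. At 30 and 180 days the likelihood score is the only perfusion readout described.

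**What a three-level score can cost**

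The article states no sample size, power or alpha for a microcirculation variable, so there is no figure to reproduce. As an illustration, take the efficiency of an ordinal score relative to a fully graded measure under proportional odds (Whitehead):

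efficiency = 1 − Σ pᵢ³, where pᵢ is the share of patients in category i

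ratio of required n = 1 / efficiency

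If the fully graded measure has 80% power at two-sided 5%, power with the score is Φ[(1.960 + 0.842) × √efficiency − 1.960].

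| Assumed split | Σ pᵢ³ | Efficiency | n ratio | Power |
|---|---|---|---|---|
| Equal thirds | 3 × 0.037 = 0.111 | 0.889 | 1.12 | 75% |
| 20/20/60 | 0.008 + 0.008 + 0.216 = 0.232 | 0.768 | 1.30 | 69% |
| 10/10/80 | 0.001 + 0.001 + 0.512 = 0.514 | 0.486 | 2.06 | 50% |
| 5/5/90 | 0.000125 + 0.000125 + 0.729 = 0.729 | 0.271 | 3.69 | 31% |

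All four splits are assumptions. Two cautions apply. The formula treats the score as a coarse version of the graded quantity. A certainty rating may follow extent less closely than that, which would make the loss larger. Conversely, a segment count also has ties, so it would recover part of the loss and not all of it.

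**Delayed enhancement (minor)**

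The rule has two classes, scar or normal. A non-enhancing zone enclosed by hyper-enhanced tissue has no class of its own and could be counted as normal, and so be left out of infarcted mass. The article gives no frequency or size for such zones, so no amount can be computed.

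**The case against.** The strongest reply is that the trial does have graded perfusion measures. Blush grade and TIMI frame count are read by an independent laboratory blinded to assignment, and the Discussion plans to correlate lymphocyte counts with angiographic parameters as well as MRI parameters. This stands for the first 24 hours. It does not reach treatment effect or change at 30 and 180 days.

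A second reply is that an ordinal score can be compared between arms and correlated. This also stands: with an even spread the loss is small. A reader might infer that, if 80 to 90% of patients scored 3, only the other 10 to 20% would carry information. That is wrong, because patients in the top category form the contrast group and contribute too. The efficiencies of 0.49 and 0.27 above are low but not negligible.

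Third, microcirculation is one of two named mechanisms, and no microcirculation variable is among the treatment comparisons listed under Study design and objectives. The point therefore concerns mechanistic analyses only.

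Fourth, a journal article condenses a fuller protocol, which may define further MRI variables. That is possible, but the article does more than stay silent: it says that defects are read by eye alone and names the score that results.

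On delayed enhancement, a reader might infer a bias against any treatment that improves microcirculation. The article does not describe such zones or how readers handle them. I would expect any effect to be smaller at 30 and 180 days, when infarcted mass is an endpoint, than at the first scan, but that is an assumption.

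**Conclusion.** The point holds in a limited form. The article promises microcirculation by MRI and fixes a readout that grades certainty instead of extent. Because the graded angiographic measures stop at 24 hours, change under treatment and correlation with lymphocytes at 30 and 180 days are poorly measured. The penalty runs from about 1.1-fold in required sample size (equal thirds) to 2.1-fold (10/10/80) and 3.7-fold (5/5/90). It rests on assumed score distributions and on proportional odds.

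It would be tempting to conclude that the microcirculation aim cannot be answered. The documents do not support that, since early graded measures exist and the score is weak but usable. The primary endpoint, LVEF at 30 days, is untouched. The enclosed-zone question is a minor point of unknown size.

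**What to change.** Have the same two blinded readers record, from the first-pass images already acquired, the number of myocardial segments with a perfusion defect at each scan. Name that count as the MRI microcirculation variable for the treatment and lymphocyte analyses, say how the two readers' counts are combined, and keep the 1 to 3 score as descriptive.

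As a minor addition, state that a non-enhancing zone enclosed by hyper-enhanced tissue counts as infarct.

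The cost is a change to the reading instructions, some extra reading time, and a blinded re-read of scans already assessed since recruitment began in May 2015. No new scans, contrast or readers are needed.
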